## Abstract

(1) Cognitive function may benefit from physical exercise in older adults. However, controversy remains over which mode of exercise is more beneficial. (2) The aim of the proposed study is to investigate the effect of open-skill exercise training on cognitive function in community dwelling older adults compared with closed-skill exercise, cognitive training, and active control. (3) One hundred and sixty participants, aged between 60 and 80 years old, will be recruited from community senior centers in Yangzhou, China and randomly assigned to one of four groups: open-skill exercise group, closed-skill exercise group, mobile game playing group, and active control group. All participants will join a 24-week program involving 50 min sessions three times a week. The primary outcome measure is visuospatial working memory. Secondary measures include subjective memory complaint, attention network, nonverbal reasoning ability, and physical activities. All participants will be measured before, mid-way, and immediately after intervention, and three months later. (4) If successful, this study is expected to provide evidence-based recommendations for older adults to select the most efficient and effective mode of exercise to improve cognitive function. Importantly, the three intervention groups provide an opportunity to separate the cognitive activity component from the physical activity component. Comparison of these components is expected to help elucidate possible mechanisms contributing to the additional cognitive benefit of open-skill exercises.

## 1. Introduction

Data issued by the National Bureau of Statistics of China indicate that there were 249 million (represent 17.9% of the total) people aged over 60 and 167 million (represent 11.9% of the total) aged over 65 in China in 2019. The prevalence of dementia in elderly people over 65 years old is 3.2–9.9% [1], which means that there are 5.3–16.5 million dementia patients in China. Cognitive function declines with aging, especially in people with neurodegenerative diseases, such as dementia and Alzheimer’s [2]. Aging-related cognitive decline and cognitive impairment impact the quality and expectancy of life in old people [3], and is of great public health and economic concern. Of note, certain types of cognitive variables remain intact, while others become impaired, with cognitive aging. Salthouse et al., (2010) demonstrated a nearly linear decline from early adulthood with respect to memory, spatial visualization, speed, and reasoning, whereas vocabulary knowledge could still increase until the age of 60 [4]. That is to say, “held” cognitive variables include vocabulary and general information in which the relevant acquisition occurred earlier in one’s life, while the “non-held” variables tend to involve the manipulation and transformation of information. Thus, the proposed study will mainly focus on aspect of cognition that decline with aging.

Cognitive function reacts sensitively to environmental changes, and can be significantly improved after certain intervention. Several studies have shown that cognitive function may benefit from physical exercise in older adults [5,6,7]. Yet, Diamond et al., (2016) argued that aerobic exercise without any cognitive component produces little or no cognitive benefit. The authors predicted that, besides direct exercise training, successful approaches should incorporate cognitive, emotional, and social needs [8]. The authors also stressed that certain modes of physical exercise, including aerobic-exercise and resistance-training, are among the least effective ways of improving executive functions [9]. Therefore, physical training should extend beyond simple moving to moving with thought [10]. Fortunately, various studies have started to focus on identifying cognitive benefit from combinations of cognitive training and physical exercise. Some studies examined these components separately, while others conducted the two components simultaneously. The separate approach usually involves cognitive trainings (e.g., focus on memory, attention, executive function, visuospatial ability), followed by physical exercise (e.g., aerobic exercise, resistance training), or vice versa [11,12,13,14,15,16]. The simultaneous approach is usually conducted in dual-tasks, such as completing the cognitive task during physical exercise [17,18,19,20] or in exergames, which combine physical exercise with computer-simulated environments and interactive videogame features [7,21]. In general, that simultaneous approach tends to have a larger effect size than the separate approach on cognition [22,23]. However, concerns exist that the similarity between cognitive assessments and dual-tasks produce a learning effect that impacts the reliability of the results. Laboratory based intervention cannot easily be generalized to everyday life of the elderly.

Thus, the present study introduces a new approach with high ecological validity by combining physical exercise and cognitive training simultaneously, specifically open-skill exercises. Open-skill exercises are defined as exercises in which participants are required to react in a dynamically changing, unpredictable, and externally environment (e.g., table tennis, badminton). In contrast, closed-skill exercises are conducted in an environment that is relatively stable, predictable, and self-paced (e.g., running and swimming) [24]. Previous studies confirmed that older adults demonstrated better executive function when participating in open-skill exercises compared to closed-skill exercises [25,26,27,28,29]. Children who played open-skill exercises also exhibited better cognitive functions and academic achievement than those who played closed-skill exercises [28,30,31]. Open-skill exercises might be advantageous because participants must mentally compare the present situation with past ones, and use this information to predict likely outcomes; consequently, participants must use their cognitive functions.

Our previous cross-sectional study on healthy older adults showed that both closed-skill and open-skill exercisers exhibited better visuospatial working memory compared to sedentary older adults. Specifically, open-skill exercises that demand higher cognitive processing exhibited selective benefits for the passive maintenance of working memory [32]. However, the cross-sectional design could only reveal a possible relationship, not a causal relationship. Additionally, the reason why open-skill exercise produces additional cognitive benefits to working memory remains unknown. Therefore, the present study protocol provides a first step to initiate an intervention study to answer the question that which type of exercise is better for older adults to decay cognitive decline. The protocol will further reveal the mechanism by setting a cognitive training group besides the open-skill and closed-skill exercise groups. Open-skill exercises can be viewed as a combination of physical exercise and cognitive training, closed-skill exercises and cognitive trainings can be viewed as pure physical exercise or cognitive training. This design may provide the opportunity to separate the physical activity component and cognitive activity component by comparing differences among the groups.

The primary objective is to investigate the effect of 24 weeks of open-skill exercise training on the cognitive function of heathy older adults in comparison to the closed-skill exercise group, cognitive training group, and control group. It is hypothesized that both training regimes will have a positive effect on cognitive function compared to the control, with the largest effect occurring in the open-skill exercise group.

## 2. Materials and Methods

### 2.1. Study Design

This study is a double-blind, 24-week randomized controlled trail (RCT) with three experimental intervention groups and an active control group. Participants will be randomly allocated to one of the four groups. The outcome measures will be performed at baseline, mid-way through intervention, immediately after intervention, and at a 3-month post-intervention follow-up. All tests and measures will be conducted by trained professionals who are blinded to the group assignment. The study design is presented in Figure 1. The schedule of enrolment, interventions, and assessments is presented in Figure 2.

The study protocol has been approved by the Ethics Committee of Yangzhou University (YXYLL-2020-106). The methods for consent were registered at Chinese Clinical Trail Registry (ChiCTR2000038733), and the data will be uploaded at the site when finishing the trial. The informed consent form will be obtained from all participants.

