### 2.4. Randomization

After signing the written informed consent, eligible participants will be randomly assigned to the active control group, and one of the three experimental intervention groups by the principal researchers. The randomization procedure will be run by an independent statistician using a computerized randomization program. The participants do not know the real purpose of the study, they are just told that they are participating in a project that aims to enrich the life of community dwelling older adults and that they are randomly allocated to different groups of the project according to a computerized randomization program. Participants and two principal researchers know the group assignments. Those who perform the intervention and outcome measures will be blinded to the allocation of participants.

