### 2.5. Interventions and Control Condition

Participants in each intervention group will be told to enroll in a 24-week program and complete 50 min sessions three times a week, and to keep their regular daily life in normal living condition. All interventions will be conducted in the community center under the supervision of personnel who will be trained by the principle researchers to ensure the standardized administration of the intervention protocols.

The intervention conditions include: (1) open-skill exercise condition, which involves a combination of physical and cognitive training, (2) closed-skill exercise condition, which involves physical exercise training alone, (3) mobile game playing condition, which is considered as cognitive training alone, (4) active control condition.

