#### 2.5.1. Open-Skill Exercise Condition

The open-skill exercise group will participate in a specially designed table tennis training program. The exercise intervention will be performed in a sequence of increasing complexity under the instruction of trainers. The trainers will be chosen from college students majoring in table tennis training.

The procedure of each single intervention session includes a warm-up, training in the basic skills of table tennis, playing table tennis with each other, special tasks designed to increase the cognitive load, and a cool down period. The aim of basic skills training is to improve general skills. It includes the following component: serving, backhand blocking, forehand attacking, left side blocking, and right side attacking (including footwork). After the coaches have demonstrated the basic skills, participants will practice with each other (or with the coaches). Training for each skill begins with simple movement, and then progresses to more complex skills, according to their degree of mastery.

To add more cognitive load to physical exercises during the process of learning the basic skills, tasks must be planned and a program of movement will be designed. This approach will be structured to achieve a particular type of training that is expected to relate to executive function. Table-tennis balls will be successively thrown to participant by a serving machine on one side of the ping-pong table. Participants stand on the other side of the table, and must anticipant the ball trajectory to intercept it. Balls are of two different colors; half are white and half are yellow. Three different tasks were designed to increase cognitive load. Participants must intercept the white ball but ignore the yellow ball in task 1, which requires inhibition function during movement. Task 2 requires participants to hit the white ball to the left side and the yellow ball to the right side across the ping-pong table. which needs task-switch ability. Task 3 was designed to train the working memory ability by asking participants to hit the ball to the left side if the previous ball is white and to the right if previous ball is yellow.

All participants will be required to move continuously during the training to maintain an average individual target heart rate reserve (HRR) of 40–59%.

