#### 2.5.3. Mobile Game Playing Condition

The cognitive training group will play a table tennis mobile game on the mobile phone without body movement. The mobile game is called Table Tennis Touch, and is a free sport action mobile multiplayer game featuring stunning graphics, intuitive swipe controls, high speed gameplay and multiple game modes developed by the British Indie Studio Yakuto. It offers a fantastic simulation of real table tennis playing settings. Players can serve, spin, and smash their way to winning. The older adults will be trained the first time, and will subsequently play under the supervision of the trainers.

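### The trial is labelled double-blind, but participants know their group and trainers deliver visibly different activities; of the parties the article names as blinded, only the outcome assessors can be

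*Protocol article*

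**What the plan says.** Section 2.1 of the protocol article gives the design label: "This study is a double-blind, 24-week randomized controlled trail (RCT) with three experimental intervention groups and an active control group". The same section says that the people who conduct the tests are blinded to group.

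Section 2.4 makes three statements about who knows what:

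- On the aim of the study: "The participants do not know the real purpose of the study". Participants are told instead of a general project to enrich community life, with random allocation to its groups.
- On the allocation: "Participants and two principal researchers know the group assignments".
- On staff: "Those who perform the intervention and outcome measures will be blinded to the allocation of participants".

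Sections 2.5 to 2.5.4 describe delivery. Sessions take place "under the supervision of personnel who will be trained by the principle researchers to ensure the standardized administration of the intervention protocols". For table tennis, "The exercise intervention will be performed in a sequence of increasing complexity under the instruction of trainers", and "The trainers will be chosen from college students majoring in table tennis training". In the phone game arm, participants are taught at the start and "will subsequently play under the supervision of the trainers". The closed-skill arm uses a cycle ergometer or treadmill, and the control arm does stretching and toning.

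Section 2.7 says that outcomes are measured by research assistants with no part in the intervention.

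**The concern.** Double-blind is a claim about a core design property. A reader normally takes it to mean that participants, and at least one other party whose behaviour could affect the result, do not know the allocation. Here the article itself says that participants do know it. It then names intervention staff as blinded, although their work consists of running one recognisable activity.

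The trial aims to give older adults evidence-based advice on which exercise to choose. Anyone who appraises or pools its results on the strength of the label would credit it with protection against performance and self-report bias that it does not have. This matters most for the outcomes that participants report themselves: memory complaint (MAC-Q) and physical activity over the past week (IPAQ). A blinded tester who hands over a questionnaire does not blind the person who fills it in. Section 2.7 also correlates MAC-Q with accuracy on the visuospatial working memory task, so the self-report enters a second planned analysis.

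**Working it through.** No arithmetic applies, because the point depends on no rate, effect size or sample size. The check sets what the article says about each party beside what the described delivery allows.

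| Party | Stated status | What the described conduct allows | Result |
|---|---|---|---|
| Participants | Know their group (2.4); unaware of the study purpose (2.4) | They do the activity themselves | Not blind to allocation |
| Two principal researchers | Know the groups (2.4) | They also train the intervention staff (2.5) | Not blind |
| Trainers and supervisors | Blinded to allocation (2.4) | They teach or supervise a visibly distinct activity (2.5 to 2.5.4) | Cannot be blind |
| Outcome assessors | Blinded (2.1, 2.4) | Separate from delivery (2.7) | Can be blind |

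1. **The label against participants.** Section 2.4 settles this directly, so the label cannot rest on participants.
2. **The label against the two staff groups in 2.4.** One could read double-blind as meaning intervention staff plus assessors. That reading needs the intervention staff to be blind. A table tennis coach demonstrates strokes and may practise with the participant; a game supervisor watches the participant play on a phone. The activity is the allocation, so the reading fails.
3. **What remains.** The assessors are said to be blinded, and their separation from delivery makes that feasible. One named party is left.
4. **Which outcomes are affected.** Section 2.6.2 lists five secondary measures: MAC-Q, the attention network test, matrix reasoning, IPAQ and the wristband. Two of the five, MAC-Q and IPAQ, are self-reports. The attention and reasoning tests, and the primary visuospatial task, are performance measures taken by blinded assessors. Steps and distance are recorded by a device.

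**The case against.** The strongest reply is that the design deals with expectancy by other means. Participants are not told the real purpose. The control is active, matched in duration and frequency, with similar social engagement across groups, and is included expressly against the Hawthorne effect. The primary outcome is accuracy and reaction time on an objective task given by blinded testers outside the intervention. Full blinding is rarely possible in exercise trials, and the article says openly that participants know their group, so an attentive reader can see the true position.

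Much of this stands. These features plausibly reduce expectancy and attention effects, and they are a reason not to overstate the consequence for the primary outcome. They do not make participants or trainers blind to allocation, which is what the article claims for the trainers. Trainers might be kept unaware of the hypothesis, but that is not what 2.4 says. Nor is this a matter of detail left to a fuller protocol, because the statements in conflict are affirmative ones in the article.

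A reader might also infer stronger faults that the article does not support:

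- *That participants learn their group before baseline testing.* Section 2.4 says only that assignment follows consent. The Figure 2 legend places baseline in week 1 but gives no time for allocation, and the flowchart and schedule are not available in the text reviewed.
- *That the principal researchers control the allocation.* Section 2.4 does have them assign participants, but it also has an independent statistician run the procedure by computer. The two can be read together, and who releases assignments is a question of concealment, not of blinding.
- *That nobody except testers could ever be blind.* A data analyst could be; the article is silent on this.
- *That the registry entry carries the same error.* That record was not seen.

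**Conclusion.** The point holds. The double-blind label in 2.1 conflicts with 2.4, and the claim in 2.4 that intervention staff are blinded conflicts with the delivery described in 2.5 to 2.5.4. As described, the trial is assessor-blinded, with participants unaware of its purpose.

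The contradiction itself is certain from the text. Its effect on results cannot be sized, since the article gives no figure for expectancy or reporting bias. In kind, two of five secondary measures have no protection from blinding. The primary outcome and the other performance tests have partial protection, although a participant's effort could still depend on knowing the group. It would go too far to infer that the primary comparison is invalid.

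The conclusion rests on two assumptions: that blinded to allocation in 2.4 has its ordinary meaning, and that the people who perform the intervention are the trainers and supervisors of 2.5 to 2.5.4. Correction is needed because the article states a core design property that the trial lacks.

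**What to change.** - **Section 2.1:** replace double-blind with assessor-blinded, with participants unaware of the study purpose.
- **Section 2.4:** limit the blinding claim to those who measure outcomes, and remove those who perform the intervention from it.
- **Section 2.6.2 or the limitations paragraph in the Discussion:** state that MAC-Q and IPAQ are reported by participants who know their group, are not protected by blinding, and will be interpreted with that limit.

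The cost is a few sentences and a less favourable blinding label. Arms, outcomes, sample size and analysis stay as they are.

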### 2.2. Participant Recruitment and Selection

Participants aged between 60 and 80 years will be recruited from the community senior centers in Yangzhou, China. Both male and female participants will be used. The older adults who are interested in participating in the research will be subject to a short interview to confirm their eligibility in the research. Potential participants will be screened using the Mini-Mental Status Examination (MMSE) [33] and exercise-related questionnaire [34].

Eligible participants are additionally required to satisfy the following criteria: (1) 60–80 years of age, (2) apparently healthy, free of cardiovascular disease, musculoskeletal problems, and psychiatric and neurological disorders, (3) normal body weight (body mass index is less than 25.0 and more than 18.5), (4) strong right handedness, (5) corrected visual acuity of at least 20/40, (6) a sedentary lifestyle, exercise at irregular base, and were assessed at the inactivity or low activity level, (7) voluntary participation in the study and willing to give written informed consent.

Participants will be excluded for any of the following: (1) objective cognitive impairment as measured by a MMSE score less than 25, (2) had experience playing table tennis in the past, (3) participated in similar research before, (4) any conflict with the objectives of this study.

### 2.3. Sample Size

The required sample size of the study was assessed by a priori power analysis (performed by G-Power). To attain a power of 0.8 (1-βerror probability), with a significant level at 0.05, 136 participants will be needed in the study.

Because the subjects are retired, older adults and due to the voluntary nature of enrollment, the attrition rate of the study is anticipated to be relatively low. When also considering other factors (such as health status, environment, and other emergency situations), a general attrition rate of 15% will be calculated in the recruitment plan task. Twenty-four additional participants will be recruited to compensate for the predicted drop-out rate, with 40 participants in each intervention condition.

To maximize compliance, the attendance and exercise performance of participants in the intervention will be monitored routinely throughout the trial.

